## 13. Trial Data

### 13.1 Baseline Photography

**Cohort 1:** Baseline photographs of the selected tumour, scheduled for excision, will be taken for reference for the 8 patients in cohort 1.

**Cohort 2:** Photographs with clearly numbered tumours will be offered to the patients so they can refer to the tumour maps to ensure the correct tumour is being treated from the correct ointment jar and kept at site for reference. Tumours will be marked with a 2mm dot using a permanent marker designed for use on skin, which the patient will renew as necessary. Tumours within the hair will have a small amount of surrounding hair trimmed to allow the patient to locate the tumour by feel, and for the volume measurements.

### 13.2 Tumour volume assessment (Cohort 2)

All tumours will be assessed for tumour volume using the Life-Viz stereoscopic imaging system by a blinded assessor (Skvara, Kalthoff et al. 2011). This is a validated system that has been shown to be a highly sensitive and reproducible method to assess skin tumour volume assessments. The device (6a) will be used to measure the volume of individual tumours (6b). The region of interest, once defined, will be measured as a base area and a raised volume compared to surrounding skin (c; i-iv). This measurement of volume will be taken at 0, 4 and 12 weeks in the trial for each tumour.

### 13.3 Blood sampling

Blood samples will be processed and stored for potential future analysis as per the lab handling manual.

### 13.4 Schedule of Patient Assessments / Data Collection

#### 14.4.1 Cohort 1

##### ***Visit 1 – Pre Screening/Baseline visit***

- Written informed consent will be taken as described in the section 10.3 of this protocol.
- Inclusion criteria will be checked and patients will be assessed to ensure they have an appropriate tumour for the trial treatment, this tumour must be scheduled for routine excision and must not be ulcerated.
- Confirmation must be recorded in the CRF that trial inclusion criteria are fulfilled and no exclusion criteria apply.

##### ***Visit 2 – Screening/Baseline visit***

The baseline visit will involve collection and retrospective collation of the following data:

- Medical history and demographics (age, gender, race)
- Tumour selected for trial treatment
- Baseline photography

- Pregnancy Test (urine), for women of child bearing potential only
- Patient reported measures: EQ5D and DLQI
- Concomitant Medication
- Confirmation must be recorded in the CRF that trial inclusion criteria are fulfilled and no exclusion criteria apply.
- Participants will be told how to apply the trial treatment and given a patient instruction sheet to take away for reference. They will also be reminded of the contact numbers stated in the patient information sheet and encouraged to call if they have any queries.
- Provide patient with Patient Diary.

### ***Visit 3a – Week – 4 End of treatment***

Visit 3 will take place at the end of treatment 4 weeks (day 28 +3days) after the entry to trial.

- Pregnancy Test (urine) , for women of child bearing potential only
- Patient treatment questionnaire
- Adverse Events
- Concomitant Medication
- Trial medication returned
- Collect completed Patient Diary

### ***Visit 3b – Surgery***

The surgery will take place at the Week 4 Visit once treatment assessment is complete

- Lesion excision

## **14.4.2 Cohort 2**

### ***Visit 1 – Pre Screening/Baseline visit***

- Written informed consent will be taken as described in the section 10.3 of this protocol.
- Inclusion criteria will be checked and patients will have appropriate tumours selected for the trial treatment.
- Confirmation must be recorded in the CRF that trial inclusion criteria are fulfilled and no exclusion criteria apply.

## ***Visit 2 – Screening/Baseline visit***

Randomisation should occur after pregnancy test and checking of inclusion/exclusion criteria. Four or five tumours will be matched for size as closely as possible and each one assigned a number to facilitate assessments and then each side of the patient allocated randomly to receive either active or placebo ointment. Jar numbers will then be allocated according to the master randomisation list.

Once patient has been randomised the trial medication can be dispensed.

The baseline visit will involve collection and retrospective collation of the following data:

- Medical history and demographics (age, gender, race)
- Baseline photography (as described in section 14.1)
- Tumour volume assessment (as described in section 14.2)
- Tumour pain assessment (log sheet and a week 0 Pain Assessment Form to be completed for each selected tumour).
- Pregnancy Test (Urine), for women of child bearing potential only
- Patient reported measures: EQ5D and DLQI (except if patient was previously in cohort 1 and a measurement exists)
- Concomitant Medication
- Patient provided with Patient Diary

## ***Week 2 - Telephone call***

- Patients will be contacted via telephone after 2 weeks to ask if they are managing the administration of the ointment and if they have any concerns or questions.

## ***Visit 3 – Week 4- Treatment assessment***

Visit 3 will take place at 4 weeks (+/- 3 days) after the randomisation date.

- Pregnancy Test (Urine) , for women of child bearing potential only
- Tumour volume assessment
- Tumour pain assessment (log sheet and a week 4 Pain Assessment Form to be completed for each selected tumour).
- Adverse Events
- Concomitant Medication
- Trial medication returned
- Trial medication dispensed (according to randomisation email at baseline)
- Patient Diary reviewed by Investigator or delegate

## ***Week 6- Telephone call***

- Patients will be contacted via telephone after 6 weeks to ask if they are still managing the administration of the ointment and if they have any concerns or questions.

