### ***Visit 4 –Week 12 - End of treatment***

The Week 12 Visit will take place at 12 weeks (+/- 3 days) after the randomisation date.

- Blood sample to be processed and stored - plasma
- Pregnancy Test (urine), for women of child bearing potential only
- Tumour volume assessment
- Tumour pain assessment (log sheet and a week 12 Pain Assessment Form to be completed for each selected tumour).
- Adverse Events
- Patient treatment questionnaire
- Concomitant Medication
- Trial medication returned
- Tumours biopsied
- Collect completed Patient Diary

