 Patient information sheet can be post to avoid any unnecessary journey

 A minimum of 24hr for review of patient information sheet before patient can sign informed consent form

 Pregnancy test should be urine dipstick and for all women of childbearing potential

### 13.8 Schedule of Events: Cohort 2

| Time                                     | Visit 1
Pre-Screening | Visit 2
Baseline visit
Confirmation of
eligibility &
Randomisation |   |   | Telephone call | Visit 3
Week 4
Treatment
Visit | Telephone call | Visit 4
Week 12
EoT | Telephone call       |
|------------------------------------------|--------------------------|--------------------------------------------------------------------------------|---|---|----------------|-----------------------------------------|----------------|---------------------------|----------------------|
|                                          | Week -1                  | Week 0                                                                         |   |   | Week 2         | Post Week 4                             | Week 6         | Post week 12              | 4 weeks post visit 4 |
| Trial Discussed / PIS given  | X                        |                                                                                |   |   |                |                                         |                |                           |                      |
| Informed Consent             |                          | X                                                                              |   |   |                |                                         |                |                           |                      |
| Photography                              |                          |                                                                                |   | X |                |                                         |                |                           |                      |
| Medical History and demographics         |                          |                                                                                | X |   |                |                                         |                |                           |                      |

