| EQ5D                         |                          |                                                                                | X |   |                |                                         |                |                           |                      |
| DLQI                         |                          |                                                                                | X |   |                |                                         |                |                           |                      |
| Patient treatment questionnaire          |                          |                                                                                |   |   |                |                                         |                | X                         |                      |
| Compliance assessment                    |                          |                                                                                |   |   | X              |                                         | X              |                           |                      |
| Volume measurement                       |                          |                                                                                |   | X |                | X                                       |                | X                         |                      |
| Tumour Pain Assessment                   |                          |                                                                                |   | X |                | X                                       |                | X                         |                      |
| Pregnancy Test               |                          |                                                                                | X |   |                | X                                       |                | X                         |                      |
| Blood sample                             |                          |                                                                                |   |   |                |                                         |                | X                         |                      |

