| Trial medication dispensed               |                          |                                                                                |   | X |                | X                                       |                |                           |                      |
| Trial medication returned                |                          |                                                                                |   |   |                | X                                       |                | X                         |                      |
| Patient Diary                            |                          |                                                                                |   | X |                | X                                       |                | X                         |                      |

|                         |  |  |   |   |  |   |  |   |   |
|-------------------------|--|--|---|---|--|---|--|---|---|
| Lesions biopsied        |  |  |   |   |  |   |  | X |   |
| Adverse events          |  |  |   |   |  | X |  | X | X |
| Concomitant medications |  |  | X |   |  | X |  | X |   |
| CRF completion          |  |  |   | X |  | X |  | X | X |

 Patient information sheet can be post to avoid any unnecessary journey

 A minimum of 24hr for review of patient information sheet before patient can sign informed consent form

 QoL only to be completed if patient was not part of the cohort 1 trial.

 Pregnancy test should be urine dipstick and for all women of childbearing potential.

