### 17.3 Protocol Specifications

For purposes of this protocol:

- All non-serious adverse reactions will be recorded at all trial visits
- Any serious adverse events will be recorded throughout the duration of the trial until the final trial visit.
- Serious adverse events exclude any pre-planned hospitalisations (e.g. elective surgery) not associated with clinical deterioration.
- Serious adverse events exclude routine treatment or monitoring of the studied indication, not associated with any deterioration in condition.
- Serious adverse events exclude elective or scheduled treatment for pre-existing conditions that did not worsen during the trial.
- Serious adverse events exclude increases in tumour size [primary outcome measure, already documented and monitored within trial]

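### Cohort 2's two on-treatment telephone calls carry no adverse event item, so direct AE questions fall only at weeks 4 and 12; adding one to each call is a cheap, modest improvement

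*Combined protocol and SAP*

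**What the plan says.** The protocol's cohort 2 visit list (14.4.2, within section 13.4) has two calls during treatment. At week 2 the patient is called "to ask if they are managing the administration of the ointment and if they have any concerns or questions". At week 6 the purpose is "to ask if they are still managing the administration of the ointment and if they have any concerns or questions".

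The schedule in 13.8 heads each of these columns "Telephone call" rather than visit. The only row ticked in them is "Compliance assessment". The row "Adverse events" is ticked at Visit 3 (week 4), Visit 4 (week 12) and the call four weeks after Visit 4. CRF completion is ticked at baseline and at those same three contacts. The visit lists agree: AEs are an item at weeks 4 and 12, and the post-treatment call asks specifically about treatment site reactions and other side effects.

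On recording, section 17.3 states: "All non-serious adverse reactions will be recorded at all trial visits". Section 17.4 is wider. It requires all AEs to be reported, and all non-serious events during drug treatment to go on the CRF.

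AEs over the 12-week treatment period are a cohort 2 secondary outcome (4.2 and 8.2.1). SAP section 7 reports them per tumour, and SAP Appendix 2 tabulates them for active against placebo.

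**The concern.** The protocol already treats a telephone call as a suitable place for direct AE questions, but uses it that way only after dosing has stopped. During dosing, the two calls rely on the patient to raise a reaction.

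Suppose a mild reaction starts soon after week 4 and settles, and the patient does not mention it. The next direct question comes at week 12. By then the patient must recall when it began, how bad it was and which tumour it affected, since the SAP wants severity, causality and tumour-level counts. Clinic review under 15.2 also starts from the patient reporting a site reaction, so a direct question would bring that review forward. Cohort 1 treats for only 4 weeks, so weeks 4 to 12 go beyond the exposure it studies in this population.

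At stake is the completeness and timing of a descriptive safety outcome. No efficacy figure is affected.

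**Working it through.** **Contacts side by side (13.8 and 14.4.2)**

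| Contact | AE row | CRF row | Compliance row | What is asked about AEs |
|---|---|---|---|---|
| Week 2 call | blank | blank | ticked | open prompt only |
| Visit 3, week 4 | ticked | ticked | blank | AE item |
| Week 6 call | blank | blank | ticked | open prompt only |
| Visit 4, week 12 | ticked | ticked | blank | AE item |
| Call 4 weeks after Visit 4 | ticked | ticked | blank | direct questions, off treatment |

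The plan states no figure for the interval, so there is none to reproduce.

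**Inputs**
- Visit 3 is day 28, range 25 to 31: "Visit 3 will take place at 4 weeks (+/- 3 days) after the randomisation date".
- Visit 4 is day 84, range 81 to 87: "The Week 12 Visit will take place at 12 weeks (+/- 3 days) after the randomisation date".
- The week 2 and week 6 calls are taken at days 14 and 42. No window is stated for either.

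**Longest gap between on-treatment AE items**
- Now: 84 − 28 = 56 days; shortest 81 − 31 = 50; longest 87 − 25 = 62.
- With a week 6 item: 84 − 42 = 42 days; shortest 81 − 42 = 39; longest 87 − 42 = 45.

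**Mean look-back from onset to the next AE item** (onset uniform within each stretch, diary ignored)
- Weeks 4 to 6, which are 14/56 = 25% of the interval: now (56 + 42)/2 = 49 days; with the item 14/2 = 7 days.
- Weeks 6 to 12, the other 75%: 42/2 = 21 days in both cases.
- All of weeks 4 to 12: now 0.25 × 49 + 0.75 × 21 = 28.0 days; with the item 0.25 × 7 + 0.75 × 21 = 17.5 days.
- A week 2 item affects weeks 0 to 4 only. Onsets in weeks 0 to 2 go from (28 + 14)/2 = 21 days to 14/2 = 7 days, and the longest gap there falls from 28 to 14 days.

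**Rough number of events that could benefit from the week 6 item.** Section 17.2 lists application site reactions at 3% and application site pruritus at 3% in earlier studies. Assume that these rates apply over 12 weeks, do not overlap, and have uniform onset.
- Patients affected: 0.06 × 15 = 0.9 to 0.06 × 20 = 1.2.
- Onset in weeks 4 to 6: × 14/84 gives 0.15 to 0.2 of a patient.
- Summing every term listed in 17.2 (44%): 0.44 × 15 × 14/84 = 1.1 to 0.44 × 20 × 14/84 = 1.5 events.

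Only the part of these that is mild, not volunteered and not noted in the diary would gain.

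**The case against.** The strongest reply is that capture is already required. The duty in 17.4 is not tied to a schedule tick, and the SAP has clinical staff record AEs directly to the database, so an AE mentioned at either call must be recorded. Asking a patient on a new ointment about concerns may well bring out a skin reaction. Patients also have a contact number (11.7.2), site reactions that they report are assessed in clinic (15.2), and week 12 has its own AE item. All of this stands. A reader might infer from the blank rows, or from the visit-based wording of 17.3, that reactions between weeks 4 and 12 go unrecorded. The documents do not support that.

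The diary is the next point. The cohort 2 grid in Appendix C is daily and by side. Its example row carries the codes S1 and S2 on runs of days that are also marked as applied, which would fit a dated symptom log. The key is not in the readable text, so this cannot be settled. If they are symptom codes, the week 12 question works from dated entries and much of the recall problem goes. Two limits remain. The visible grid has one row per side, whereas the SAP reports per tumour. And the visit lists place diary review at week 4 and collection at week 12, with no look in between.

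A reader might also infer that the active-versus-placebo AE table is biased. Both sides belong to the same blinded patient and are asked about at the same contacts. The documents give no reason to expect recall to differ by side.

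Finally, the gain is small. Few events are expected in weeks 4 to 6, AE reporting is descriptive without significance testing, and the Phase 2a decision rests mainly on response (SAP 8.4). That is fair, and it sets the priority of the point. It does not explain why direct questions are asked by telephone after treatment but not during it.

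**Conclusion.** The point holds as a low-priority, cheap improvement. Direct on-treatment AE questions in cohort 2 come only at weeks 4 and 12, nominally 56 days apart (50 to 62), although two calls already take place during treatment.

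The benefit is limited to earlier and more direct ascertainment, and earlier clinic review, of mild or transient reactions. For weeks 4 to 12 it falls entirely on onsets in weeks 4 to 6, and a 42-day gap from week 6 to week 12 remains. Because the look-back means ignore the diary, read them as upper bounds on the recall burden; they also assume uniform onset. They count days, not missed events, and any under-count cannot be estimated from the documents. Neither missing safety reporting nor bias between sides is shown.

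**What to change.** - In 13.8 and 14.4.2, tick the AE and CRF completion rows at the week 2 and week 6 calls. If only one is taken up, choose week 6, because it alone shortens the 56-day gap.
- Ask the site-reaction and side-effect questions of the post-treatment call, reworded to cover the time since the last contact. Record the answers by tumour number and side.
- Extend the recording rule in 17.3 to scheduled telephone calls, so that it agrees with the schedule and with 17.4.

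No extra contact and no new SAP table is needed. The cost is a few minutes and one CRF page per call: 2 × 15 = 30 to 2 × 20 = 40 pages over 15 to 20 patients. Add to that a protocol amendment and small updates to the eCRF and the data management plan.

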### ***Visit 4 –Week 12 - End of treatment***

The Week 12 Visit will take place at 12 weeks (+/- 3 days) after the randomisation date.

- Blood sample to be processed and stored - plasma
- Pregnancy Test (urine), for women of child bearing potential only
- Tumour volume assessment
- Tumour pain assessment (log sheet and a week 12 Pain Assessment Form to be completed for each selected tumour).
- Adverse Events
- Patient treatment questionnaire
- Concomitant Medication
- Trial medication returned
- Tumours biopsied
- Collect completed Patient Diary

### ***Telephone call (4 week follow up)***

Participants will be contacted by telephone 4 weeks after completing the trial to ensure there have been no further significant adverse events during this period. They will be asked if they have experienced any treatment site reactions since stopping treatment, or any other side effects. If necessary an appointment will be made for the participant to have a follow up visit in clinic for assessment and management.

## **13.5 Tumour Biopsies**

**Cohort 1:** At the end of treatment visit, week 4, the routinely excised tumour will undergo routine analysis and some of the sample will be snap frozen and stored. This sample will be stored with a view to developing a CT327 skin assay. Participants will have the option to consent to samples potentially being used in future studies relating to the title of this trial.

**Cohort 2:** At the end of treatment visit, week 12, one tumour that has been treated with active treatment and one tumour that has been treated with placebo will be biopsied to assess histological and immunohistochemical changes. A proportion of these samples will be stored with the potential to undergo CT327 analysis in the future.

## **13.6 Immunohistochemical Analyses and gene expression profiling**

A secondary endpoint is histological and immunohistochemical changes, and the two biopsied samples from cohort 2 will be analysed to assess such changes.

These tumour samples will be assessed by a pathologist that is blinded to the treatment applied to the specimens. Immunostaining with phosphorylated forms of the MAP kinase pathway and BCL2 (an antiapoptotic protein) will be assessed to determine if TRK inhibition is leading to anticipated cell death via suppression of the expected downstream targets of

TRK. Tissue concentrations of CT 327 will also be assessed in a representative portion of samples.

To fulfil the secondary objective for cohort 2, delineate the mechanism by which TRK inhibition exerts an effect on tumour volume, the following procedures will be performed

Gene expression profiling of tumour samples to compare placebo and control treated samples. Tumours will be assessed for changes following TRK inhibition using RNA sequencing to obtain changes in transcripts between placebo and CT327 treated tumours. A total of 12 treated and 12 placebo tumours will be assessed, which we plan to obtain from the 15-20 recruited patients. This will give insight into the effects of TRK inhibition in a CYLD defective tumour model, which will inform the mechanistic understanding of this treatment in skin tumours.

### 13.7 Schedule of Events: Cohort 1

| Time                                     | Visit 1
Pre-Screening | Visit 2
Baseline visit
Confirmation of eligibility |   |   | Visit 3a
Week 4 EoT | Visit 3b
Surgery  |
|------------------------------------------|--------------------------|----------------------------------------------------------|---|---|------------------------|----------------------|
|                                          | —                        | Week 0                                                   |   |   | 28 days
(+3 days)   | 28 days
(+3 days) |
| Trial Discussed / PIS given  | X                        |                                                          |   |   |                        |                      |
| Informed Consent             |                          | X                                                        |   |   |                        |                      |
| Photography                              |                          |                                                          |   | X |                        |                      |
| Medical History and demographics         |                          |                                                          | X |   |                        |                      |
| EQ5D                                     |                          |                                                          | X |   |                        |                      |
| DLQI                                     |                          |                                                          | X |   |                        |                      |
| Patient treatment questionnaire          |                          |                                                          |   |   | X                      |                      |
| Pregnancy Test               |                          |                                                          |   | X | X                      |                      |
| Trial medication dispensed               |                          |                                                          |   | X |                        |                      |
| Trial medication returned                |                          |                                                          |   |   | X                      |                      |
| Patient diary                            |                          |                                                          |   | X | X                      |                      |
| Lesion Excision                          |                          |                                                          |   |   |                        | X                    |
| Adverse events                           |                          |                                                          |   |   | X                      |                      |
| Concomitant medications                  |                          |                                                          | X |   | X                      |                      |
| CRF completion                           |                          |                                                          |   | X | X                      |                      |

 Patient information sheet can be post to avoid any unnecessary journey

 A minimum of 24hr for review of patient information sheet before patient can sign informed consent form

 Pregnancy test should be urine dipstick and for all women of childbearing potential

### 13.8 Schedule of Events: Cohort 2

| Time                                     | Visit 1
Pre-Screening | Visit 2
Baseline visit
Confirmation of
eligibility &
Randomisation |   |   | Telephone call | Visit 3
Week 4
Treatment
Visit | Telephone call | Visit 4
Week 12
EoT | Telephone call       |
|------------------------------------------|--------------------------|--------------------------------------------------------------------------------|---|---|----------------|-----------------------------------------|----------------|---------------------------|----------------------|
|                                          | Week -1                  | Week 0                                                                         |   |   | Week 2         | Post Week 4                             | Week 6         | Post week 12              | 4 weeks post visit 4 |
| Trial Discussed / PIS given  | X                        |                                                                                |   |   |                |                                         |                |                           |                      |
| Informed Consent             |                          | X                                                                              |   |   |                |                                         |                |                           |                      |
| Photography                              |                          |                                                                                |   | X |                |                                         |                |                           |                      |
| Medical History and demographics         |                          |                                                                                | X |   |                |                                         |                |                           |                      |
| EQ5D                         |                          |                                                                                | X |   |                |                                         |                |                           |                      |
| DLQI                         |                          |                                                                                | X |   |                |                                         |                |                           |                      |
| Patient treatment questionnaire          |                          |                                                                                |   |   |                |                                         |                | X                         |                      |
| Compliance assessment                    |                          |                                                                                |   |   | X              |                                         | X              |                           |                      |
| Volume measurement                       |                          |                                                                                |   | X |                | X                                       |                | X                         |                      |
| Tumour Pain Assessment                   |                          |                                                                                |   | X |                | X                                       |                | X                         |                      |
| Pregnancy Test               |                          |                                                                                | X |   |                | X                                       |                | X                         |                      |
| Blood sample                             |                          |                                                                                |   |   |                |                                         |                | X                         |                      |
| Trial medication dispensed               |                          |                                                                                |   | X |                | X                                       |                |                           |                      |
| Trial medication returned                |                          |                                                                                |   |   |                | X                                       |                | X                         |                      |
| Patient Diary                            |                          |                                                                                |   | X |                | X                                       |                | X                         |                      |

|                         |  |  |   |   |  |   |  |   |   |
|-------------------------|--|--|---|---|--|---|--|---|---|
| Lesions biopsied        |  |  |   |   |  |   |  | X |   |
| Adverse events          |  |  |   |   |  | X |  | X | X |
| Concomitant medications |  |  | X |   |  | X |  | X |   |
| CRF completion          |  |  |   | X |  | X |  | X | X |

 Patient information sheet can be post to avoid any unnecessary journey

 A minimum of 24hr for review of patient information sheet before patient can sign informed consent form

 QoL only to be completed if patient was not part of the cohort 1 trial.

 Pregnancy test should be urine dipstick and for all women of childbearing potential.

